### Participants

The sample of parents will be derived from couples attending antenatal classes at one of the participating hospitals. For couples to be eligible to participate they must own a compatible smartphone, have internet access, reside within WA, both partners must intend to participate in the rearing of their child and have sufficient English language skills to engage with the intervention. Couples will be ineligible where existing medical conditions in the mother are likely to inhibit the initiation of breastfeeding or exclusive breastfeeding or if they are a same sex couple.

### Recruitment

Recruitment will take approximately 18 months, allowing for a wash-out period between each intervention arm in each hospital. The *MI1* and *HI* being hospital-based require access to antenatal classes. Usually antenatal classes run for a month and there is little overlap between classes. Each hospital has a series of antenatal classes and most metropolitan hospitals have at least 2 classes per week occurring on different days. As the researchers will be conducting the special antenatal classes and as the social support intervention happens externally to the hospital we are confident that there will be no leakage between intervention and control participants. Nevertheless, to ensure there is no contamination a washout period will be incorporated in the *MI1* and *HI* interventions.

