**Methods/design:**

The PIFI study is a factorial randomised controlled trial. Participants will be mothers and their male partners attending antenatal classes at selected public and private hospitals with maternity departments in Perth, Western Australia. Fathers will be randomly allocated to either the usual care control group *(CG)*, one of two medium intensity (*MI1* and *MI2*) interventions, or a high intensity (*HI*) intervention. *MI1* will include a specialised antenatal breastfeeding education session for fathers with supporting print materials. *MI2* will involve the delivery of an antenatal and postnatal social support intervention delivered via a smartphone application and *HI* will include both the specialised antenatal class and the social support intervention. Outcome data will be collected from couples at baseline and at six and 26 weeks postnatally. A total of 1600 couples will be recruited. This takes into account a 25 % attrition rate, and will detect at least a 10 % difference in the proportion of mothers breastfeeding between any two of the groups at 26 weeks at 80 % power and 5 % level of significance, using a Log-rank survival test. Multivariable survival and logistic regression analyses will be used to assess the effect of the treatment groups on the outcomes after adjusting for covariates.

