### The interventions

The *Medium Intensity Intervention 1* (*MI1*) and the *High Intensity Intervention* (*HI*) groups will include a specialised antenatal breastfeeding education session for fathers. These sessions will be held in conjunction with antenatal classes at the participating hospitals and will require fathers to attend an additional class focusing on fatherhood, breastfeeding and anticipatory problem solving. These three key issues (importance of breastfeeding, the positive role of fathers and problem solving), were identified from the process evaluation of the FIFI study [41, 42], a review of earlier international programs and assessment of what was realistic to implement in the existing system. The class format and developed materials have been evaluated and refined during the FIFI study [42]. The educational intervention will focus on reducing fathers’ reservations about breastfeeding, reducing negative attitudes, building skills and knowledge and providing social support strategies. Specific take-home print materials to be shared by both partners will be developed that support the anticipatory problem solving component of the session. Training will be provided for the male antenatal educators in order to standardise the delivery of antenatal classes across hospitals.

From the time they are recruited, fathers randomised into either the *Medium Intensity Intervention 2* (*MI2*) or the *High Intensity Intervention* groups (*HI)* will receive sequenced, motivational, social support and educational material that will include ‘trouble shooting’ suggestions for handling common breastfeeding related difficulties (e.g. engorgement, attachment and sleep interruption), how to deal with interpersonal issues (e.g. body image and sexuality) and other life event issues (e.g. going back to work). Tips for providing practical and emotional support and caring for the mother (e.g. recognising the signs and symptoms of postnatal depression) and information on infant developmental milestones will be included. Conversational topics reinforcing these educational and motivational materials, resources and services will be ‘pushed’ out to fathers via a smartphone application from time of recruitment until 26 weeks postnatal. Push notifications delivered via the smartphone application will contain links to a library of more detailed web-based materials which fathers will be encouraged to share and discuss with their partner.

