### Randomisation

Randomisation will be determined through a computer-based random sequence generator. Participants will not be blinded to the true nature of the study, nor will researchers be blinded to participants’ group allocation, however the study statistician will analyse the data independently and hence will be blinded to the allocation of participants to groups.

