### Ethical considerations

Participants will be provided with verbal and written information describing the purpose of the intervention and what their participation will involve. They will be advised that they may decline to participate without prejudice. Written informed consent will be obtained from both partners prior to randomisation into a study arm. They will be assigned a unique ID number which will link partners and their baseline and follow-up questionnaires.

When agreeing to participate in the study participants will be assured of anonymity and confidentiality. They will be requested to provide their name, address, email and phone number so that they can be followed-up by phone call, short message service (SMS) and email. Any woman who declines to participate in the study will be requested to anonymously provide basic demographic information, including age, years of education, marital status and intended method of feeding. It will be explained that this basic information will be used only to determine if the final sample is representative of new mothers and fathers in general. The right of non-participants to decline to provide this information will be respected.

The project has been approved by the Curtin University Human Research Ethics Committee (HR 82/2014; 14 May 2014) and the Human Research Ethics Committees responsible for the public (SCGG HREC No 2014–111; 18 Sept 2014) and private (SJGHC Ref: 777; 8 April 2015) hospital sites.

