### Statistical considerations

#### Sample size

The key outcome variable for statistical analysis is duration of breastfeeding. It is assumed that at 26 weeks, there is at least a 10 % difference in the proportion of mothers’ breastfeeding between any two of the groups. A sample size of 300 participants (fathers) is required in each of the 3 intervention groups and control group to be able to detect the difference at 80 % power and 5 % level of significance, using a Log-rank survival test. Assuming a loss to follow-up of 25 % in each group, a total of 400 participants for each group will be recruited (Total n recruited = 1600 couples, total n required =1200). The sample size was calculated in terms of the hazard ratio taking into account the censoring of data, as survival analysis will be used for the analysis of time to breastfeeding cessation, the main outcome variable.

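### Individual randomisation and a wash-out between arms within each hospital do not fit together: the unit of allocation must be settled, because the sample size counts independent participants

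*Protocol article*

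**What the plan says.** Most of the protocol article describes individual allocation. The abstract says "Fathers will be randomly allocated to either the usual care control group" or one of the intervention groups. The Ethical considerations section says "Written informed consent will be obtained from both partners prior to randomisation into a study arm". The section on the interventions also speaks of fathers being randomised into MI2 or HI, and the Study design section cites the reporting guideline for parallel group trials.

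The Recruitment section reads differently. The 18-month recruitment period is set "allowing for a wash-out period between each intervention arm in each hospital". The section notes that a class series lasts about a month, that series overlap little, and that most metropolitan hospitals run at least two classes a week on different days. It ends by saying that "to ensure there is no contamination a washout period will be incorporated in the" MI1 and HI interventions, which is narrower than its opening sentence.

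The Randomisation section says only this about method: "Randomisation will be determined through a computer-based random sequence generator". It names no unit, block, stratum or period.

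The Sample size section says "A sample size of 300 participants (fathers) is required in each of the 3 intervention groups and control group". The allowances it names are the hazard ratio, censoring and 25 % loss to follow-up. On delivery of the MI1 and HI education, the article says "These sessions will be held in conjunction with antenatal classes at the participating hospitals".

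**The concern.** A wash-out between arms separates them in time. If couples at a hospital are randomised one by one to four arms that are all open, there is no gap between arms in which to place it. The remarks on class length and overlap also matter mainly if arm is tied to a class series or period. So the Recruitment section implies, without saying so, that at least MI1 and HI are allocated by class or by period.

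Three things would follow from that.

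- **Confounding.** Within a hospital, arm would be confounded with calendar time: season, staff and case-mix. More couples would not remove this.
- **Foreseeable allocation.** If one arm is open at a time, those recruiting may be able to foresee it when they seek consent.
- **Precision.** Couples in the same class or period share influences. The 300 per arm would then carry less information than 300 independent couples, and a log-rank or Cox analysis that ignores this would understate the standard errors.

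Even with allocation by couple, fathers in MI1 and HI share an education session, so a milder form of the third problem remains in those two arms.

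**Working it through.** **1. The plan's own figures.** Inputs from Sample size: 300 per arm, 25 % loss, four arms. 300 / (1 − 0.25) = 400 per arm, and 400 × 4 = 1600. This is exact, so the step from 300 to 400 is used up by loss alone and contains no design effect.

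The 300 itself cannot be uniquely reproduced, because the control proportion and hazard ratio are not given. With HR = ln(p_trt)/ln(p_ctrl), a 10-point difference, two-sided 5 % and 80 % power, the Schoenfeld formula gives a value within 3 % of 300 for control proportions of about 0.25 to 0.275 or 0.67 to 0.695. A formula for independent observations therefore yields 300 for some base rates, and no design effect is needed to explain it.

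**2. Assumptions for the illustration.** The article gives no ICC and no class size. I assume classes of m = 10 couples and ICC from 0.01 to 0.05. I also take 300 independent couples per arm to give exactly 80 % power, so that the loss shown is due to clustering only.

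**3. If arm follows the class (all arms clustered).**

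- Design effect DE = 1 + (m − 1) × ICC: 1 + 9 × 0.01 = 1.09, and 1 + 9 × 0.05 = 1.45.
- Effective n per arm = 300 / DE: 300/1.09 = 275, and 300/1.45 = 207.
- Type I error of an unadjusted test = 2 × [1 − Φ(1.96/√DE)]: 6.0 % and 10.4 %.
- Power = Φ[(1.96 + 0.842)/√DE − 1.96]: 76.5 % and 64.3 %.
- Couples needed to restore 80 %: 300 × DE = 327 and 435 per arm before loss. Dividing by 0.75 gives 436 and 580 per arm, or 1744 and 2320 in total.

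Larger hospital-period clusters would give larger design effects at the same ICC, but the article gives no basis for their size.

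**4. If allocation is by couple (only MI1 and HI share the special session).** For MI1 or HI against control, one arm is clustered and the other is not, so the variance inflation is the average of DE and 1.

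- Inflation: (1.09 + 1)/2 = 1.045, and (1.45 + 1)/2 = 1.225.
- Type I error by the same formula: about 5.5 % and 7.7 %.
- MI2 against control has no clustering from the special session.

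**5. What arithmetic cannot show.** The confounding of arm with calendar time in the first case is a bias. Its size and direction cannot be derived from the document.

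**The case against.** The strongest reply is that the article never says that arms run one at a time. It speaks repeatedly of randomising fathers or couples, it places consent before randomisation, and the closing sentence of Recruitment confines the wash-out to the two class-delivered arms. MI2 is delivered outside the hospital and control is usual care, so neither needs a wash-out. Gaps around the MI1 and HI class series, with the other arms running alongside, are a possible reading. This stands: a reader might infer strict one-arm-at-a-time blocks with the arm known before consent, but the document does not support stating that as fact. It does not remove the conflict, because even the narrower reading ties MI1 and HI to a class series or period, which is not individual allocation to arms open together.

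A reader might also infer very large errors by assuming big hospital-period blocks. The document gives no block size, number of hospitals or ICC, so such figures would be speculation. Nor should a power below 80 % that comes from picking a base rate be blamed on clustering. At 50 % against 60 %, for example, 300 per arm gives about 71 % power with fully independent couples.

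Third, the covariate list under Data analyses is explicitly open, and an analysis plan that is not shown could add hospital, period or a cluster-robust variance. That also stands, so their absence from a condensed article is not the finding. But an analysis plan cannot decide which allocation statement is true, and the basis of the 300 is set in this article.

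Last, if the special session has no effect in any class, sharing it adds no correlation, and under individual randomisation the background hospital effects are balanced between arms. The by-couple branch is therefore mild.

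**Conclusion.** The point holds as a contradiction about the unit of allocation, with consequences that depend on how it is resolved. The abstract, the section on the interventions and Ethical considerations describe individual allocation. Recruitment implies that at least MI1 and HI are separated by class series or period within a hospital, and it is not consistent with itself on which arms the wash-out covers. Randomisation does not settle the matter.

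If arm follows class or hospital-period, arm is confounded with calendar time, allocation may be foreseeable at consent, and the stated 300 per arm and 80 % power do not hold. On the assumed classes of 10 and ICC 0.01 to 0.05, the unadjusted type I error is about 6 to 10 % and the power about 77 to 64 %. If allocation is by couple, the type I error for MI1 or HI against control is about 5.5 to 7.7 % on the same assumptions. The conflict itself is certain. The sizes are illustrations, because the document gives neither ICC nor cluster size.

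**What to change.** State one unit of allocation and make Recruitment, Randomisation, Ethical considerations, the section on the interventions and the abstract agree with it, including which arms the wash-out covers.

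- **If the unit is the class or hospital-period:** randomise at that level. Stratify or adjust the Cox model for hospital and calendar period. Use a shared frailty or a cluster-robust variance with that unit as the cluster. Restate the power with a design effect, giving the assumed ICC and cluster size.
- **If the unit is the couple:** remove or explain the wash-out between arms. Stratify the Cox model by hospital, and allow for clustering by special class in MI1 and HI only.

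The cost is protocol wording and some analysis work, with wider confidence intervals and a lower stated power. No extra couples are needed for the correction. Restoring 80 % under class-level allocation would need the larger totals shown above, so the proposal is to report the lower power openly rather than to enrol more.

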### The interventions

The *Medium Intensity Intervention 1* (*MI1*) and the *High Intensity Intervention* (*HI*) groups will include a specialised antenatal breastfeeding education session for fathers. These sessions will be held in conjunction with antenatal classes at the participating hospitals and will require fathers to attend an additional class focusing on fatherhood, breastfeeding and anticipatory problem solving. These three key issues (importance of breastfeeding, the positive role of fathers and problem solving), were identified from the process evaluation of the FIFI study [41, 42], a review of earlier international programs and assessment of what was realistic to implement in the existing system. The class format and developed materials have been evaluated and refined during the FIFI study [42]. The educational intervention will focus on reducing fathers’ reservations about breastfeeding, reducing negative attitudes, building skills and knowledge and providing social support strategies. Specific take-home print materials to be shared by both partners will be developed that support the anticipatory problem solving component of the session. Training will be provided for the male antenatal educators in order to standardise the delivery of antenatal classes across hospitals.

From the time they are recruited, fathers randomised into either the *Medium Intensity Intervention 2* (*MI2*) or the *High Intensity Intervention* groups (*HI)* will receive sequenced, motivational, social support and educational material that will include ‘trouble shooting’ suggestions for handling common breastfeeding related difficulties (e.g. engorgement, attachment and sleep interruption), how to deal with interpersonal issues (e.g. body image and sexuality) and other life event issues (e.g. going back to work). Tips for providing practical and emotional support and caring for the mother (e.g. recognising the signs and symptoms of postnatal depression) and information on infant developmental milestones will be included. Conversational topics reinforcing these educational and motivational materials, resources and services will be ‘pushed’ out to fathers via a smartphone application from time of recruitment until 26 weeks postnatal. Push notifications delivered via the smartphone application will contain links to a library of more detailed web-based materials which fathers will be encouraged to share and discuss with their partner.

The Control Group *(CG)* will receive the standard breastfeeding support which will include information provided by hospital antenatal education programs and in-hospital breastfeeding support. All parents will be free to attend other antenatal classes or seek other breastfeeding assistance from the community. Uptake of these additional activities will be measured via the postnatal six and 26 week surveys.

### Randomisation

Randomisation will be determined through a computer-based random sequence generator. Participants will not be blinded to the true nature of the study, nor will researchers be blinded to participants’ group allocation, however the study statistician will analyse the data independently and hence will be blinded to the allocation of participants to groups.

### Ethical considerations

Participants will be provided with verbal and written information describing the purpose of the intervention and what their participation will involve. They will be advised that they may decline to participate without prejudice. Written informed consent will be obtained from both partners prior to randomisation into a study arm. They will be assigned a unique ID number which will link partners and their baseline and follow-up questionnaires.

When agreeing to participate in the study participants will be assured of anonymity and confidentiality. They will be requested to provide their name, address, email and phone number so that they can be followed-up by phone call, short message service (SMS) and email. Any woman who declines to participate in the study will be requested to anonymously provide basic demographic information, including age, years of education, marital status and intended method of feeding. It will be explained that this basic information will be used only to determine if the final sample is representative of new mothers and fathers in general. The right of non-participants to decline to provide this information will be respected.

The project has been approved by the Curtin University Human Research Ethics Committee (HR 82/2014; 14 May 2014) and the Human Research Ethics Committees responsible for the public (SCGG HREC No 2014–111; 18 Sept 2014) and private (SJGHC Ref: 777; 8 April 2015) hospital sites.

### Data collection

#### Data collection instruments

Questionnaires will be developed utilising questions previously validated in the FIFI study [36] and the first and second Perth Infant Feeding Studies [22, 43], with new items tested for face and content validity. The baseline and follow-up questionnaires will include a number of previously validated and widely used instruments to measure psychosocial factors associated with breastfeeding outcomes. These will include, but are not limited to, the Iowa Infant Feeding Attitude Scale [44], the Breastfeeding Self-Efficacy Scale [45], the Postpartum Partner Support Scale [46], the Child Care Stress Checklist [47] and the Depression Anxiety Scale (DASS-21) [48].

#### Data collection procedures

Both partners will self-complete a questionnaire at baseline and will complete follow up questionnaires either online or by telephone at six and 26 weeks postnatally. In addition, all participating mothers will complete a brief questionnaire delivered on-line or by SMS at 12 and 18 weeks to determine current breastfeeding status. Process evaluation will be conducted to assess the fidelity and quality of implementation, with an emphasis upon measuring dose and utility, and to assess the adherence and proficiency of the facilitators delivering the antenatal classes.

### Primary outcomes

Duration of any breastfeedingDuration of exclusive breastfeeding

### Secondary outcomes

Age of introduction of formulaAge of introduction of complementary foods (‘solids’)Infant feeding attitudes of both partners.Maternal breastfeeding self-efficacy

### Statistical considerations

#### Sample size

The key outcome variable for statistical analysis is duration of breastfeeding. It is assumed that at 26 weeks, there is at least a 10 % difference in the proportion of mothers’ breastfeeding between any two of the groups. A sample size of 300 participants (fathers) is required in each of the 3 intervention groups and control group to be able to detect the difference at 80 % power and 5 % level of significance, using a Log-rank survival test. Assuming a loss to follow-up of 25 % in each group, a total of 400 participants for each group will be recruited (Total n recruited = 1600 couples, total n required =1200). The sample size was calculated in terms of the hazard ratio taking into account the censoring of data, as survival analysis will be used for the analysis of time to breastfeeding cessation, the main outcome variable.

